**Figure 3 figure3:**
[figure not shown]
Overall flow of the CoDuBu study (Swiss TPH: Swiss Tropical and Public Health Institute; IPCI: Institut Pasteur de Côte d’Ivoire).

### Sample Size Estimation and Sampling of Participants

For the descriptive cross-sectional study, using *Plasmodium* infection and diabetes as our disease co-occurrence of reference, we would expect a malaria prevalence of 30% [59] and diabetes prevalence of 6% [60] in adults. The expected prevalence of co-occurrence assuming independence was 2%. The health district of Tiassalé, where Taabo HDSS is located, has an estimated population of 200,000 [33]. Therefore, for a population of 200,000, with an error margin of 1%, a 95% confidence level, and an expected malaria and diabetes co-occurrence prevalence of 2%, we would need 751 participants. Assuming a nonresponse rate of 30%, the sample size becomes 976. A sample size of 1000 would therefore be enough for the descriptive baseline study.

A main hypothesis to be addressed in an envisaged, not-yet funded follow-up survey, would be that the average change in HbA1c would be higher in persons malaria-positive at baseline. For the power calculation, we assume a malaria positivity rate of 30% and a true difference in average change of HbA1c between malaria-positive and negative persons of at least 30% of the standard deviation (SD) sigma of individual changes. If these individual changes were normally distributed, this would mean that the median of change in malaria-positive persons coincides with the 62^nd^percentile in malaria-negative persons. Under this assumption, 560 persons being re-assessed for HbA1c at follow-up would provide a power of 90% to detect a statistically significant difference in the mean change of HbA1c between the two groups at the usual 5% level. However, a larger sample size is warranted in order to be able to compensate for potential reductions in statistical efficiency resulting from lower than expected malaria positivity prevalence or from variations in the prevalence of malaria-positivity or in the SD sigma across the three study sites. With 30% loss to follow-up, we would still have 700 persons to be re-assessed at follow-up, which would provide a moderate safety margin and allow for the adjustment of weak confounder variables. Therefore, the 1020 participants we sampled from the three selected areas of Taabo HDSS will enable adequate representation of the population and ensure enough statistical power to test our hypotheses.

A random sampling technique was used to select about 2000 participants satisfying the inclusion criteria in the three selected sites. The inclusion criteria included (1) registration in the Taabo HDSS, (2) residence in Taabo-Cité, Amani-Ménou, or Tokohiri, (3) one adult per household, and (4) age ≥18 years. Stratified sampling technique was applied to select 513, 254, and 253 participants from Taabo-Cité, Amani-Ménou, and Tokohiri respectively (ratio of 2:1:1). This corresponds to the overall distribution of adults (Taabo-Cité=3905, Amani-Ménou=2094, Tokohiri=1626) and households (Taabo-Cité=1508, Amani-Ménou=567, Tokohiri=616) in the three areas. Selected participants from each stratum were then invited for participation in a random fashion until the target sample size in each site was reached.

### Recruitment of Participants and Written Informed Consent

After an information event for the village population, informed consent from potential participants was obtained at their homes, in-person by HDSS field workers who are in close contact with the local population. In order to obtain written informed consent, the field workers explained the purpose, procedures, benefits, and potential harm of the study. The concept of establishing a biobank for future studies was also explained, and participants were made aware that their information would be treated in a coded manner to allow the establishment of a longitudinal study if they decided to participate. The voluntary nature of the study was explained to the participants. Participation in all or parts of the study, as well as nonparticipation was free of negative consequences. Sufficient time for asking questions on the aims and procedures of the study was provided to the participants. If a subject decided to participate, they signed the informed consent sheet. Illiterate participants put a cross in the presence of a literate witness. Consent for re-contact in the future was specifically obtained from all participants towards the establishment of a longitudinal cohort.

### Assessment of Health-Related Phenotypes

Textbox 1 summarizes the health-related phenotypes expected from the study. These phenotypes will be derived from physical examinations; laboratory analyses of venous blood, urine, and stool; and in-person interviews with a questionnaire.

### Physical Examination

Body temperature was measured with an Omron auricular thermometer (Omron Healthcare). Systolic and diastolic blood pressure were measured three times, at least 3 minutes apart, after sitting quietly for about 10 minutes, using an Omron Oscillograph (Omron Healthcare). The mean of the last two measurements will be taken for analyses. Hypertension will be defined as a mean systolic blood pressure ≥140 mm Hg or mean diastolic blood pressure ≥90 mm Hg.

Height and weight were measured using a SECA bodymeter (0.1 cm accuracy) and weighing scale (0.1 kg accuracy), respectively. Precision of the bodymeter was checked regularly by measuring the height of the placement of the bodymeter using a tape rule, and the weighing scale was verified using a known 10 kg weight. Neck circumference was measured using a SECA ergonomic tape below the laryngeal prominence in front and the mid-cervical spine behind. Mid-arm circumference was measured at the midpoint between the shoulder and the elbow. Waist circumference was measured at the end of passive expiration over the narrowest part of the trunk between the lowest rib and the iliac crest, or if this is not clearly evident, at the level of the umbilicus. Hip circumference was measured using the same tape, at the maximal circumference between the iliac crest and the crotch. Waist circumference, waist-hip ratio, and body mass index will be described in absolute values and categorized according to various guidelines [61].

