### Objectives of the CoDuBu Study

The overarching goal of this project is to deepen our understanding of the dual burden of IDs (helminthiases and malaria) and NCDs (hypertension and diabetes) among adults in the Taabo HDSS in south-central Côte d’Ivoire, to set the stage for future mechanistic research, and to translate key findings into policy action. We will pursue the following specific objectives:

To conduct a population-based cross-sectional survey in adults from rural and semi-urban parts of the Taabo subdistrict to assess (a) the prevalence, intensity, and distribution of helminth (*Ascaris lumbricoides*, *S. stercoralis*, hookworm, *Trichuris trichiura*, *Schistosoma haematobium,* and *Schistosoma mansoni*) and *Plasmodium* infections, (b) the prevalence and distribution of metabolic syndrome, hypertension, and diabetes, and (c) the co-occurrence of these IDs and NCDs and the distribution of these comorbidities and their respective risk factors at the level of individuals.To establish a biobank consisting of blood, urine, and stool as an investment for future longitudinal biomarker research on the mechanistic link between helminth and *Plasmodium* infections, and hypertension and diabetes.To prepare the local health system for the uptake and management of NCDs through assessment of deficiencies and provision of necessary training, instruments, and facilities to the local health staff and health centers.

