In Phase II (interview; June-August 2017), participants were interviewed on a third day, following health examinations. Interviews assessed among other factors, sociodemographic characteristics, health status, ID and NCD risk factors, medication and vaccination history, health care use, as well as knowledge and attitudes regarding NCDs.

Two study teams of about 10 persons each were responsible for the conduct of the study. The teams included 1 research staff (supervision of adherence to study protocol), 1 medical doctor (supervision of physical examination), 3 study nurses (conduct physical examination and point-of-care tests), 1 laboratory supervisor (supervision of work-up and analyses of biospecimens), 1-2 laboratory technicians (work-up and analyses of biospecimens), 2 HDSS field staff speaking the local language(s) and resident in the study area (informed consent, instruction for home biospecimen collection and health interviews), and 1 driver.

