### In-Person Interviews

The in-person interviews were done using a tablet-based questionnaire in Open Data Kit format [67], lasting between 45 and 60 minutes. Questions covered demographic factors (eg, age, sex), water supply and sanitation facilities (availability and use), know-how, attitude, and behavior towards tobacco smoking, physical activity, obesity, alcohol consumption, and nutrition. They also included environmental risks (eg, exposure to mosquito coils, pesticides, indoor biomass fuels), gender, hormonal and reproductive factors, psychosocial stressors and resilience to them, disease symptoms (respiratory, cardiovascular, and diabetes), family history of disease, medical diagnoses and treatments, vaccination history, and access to health care.

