### Data Analyses

The detailed CoDuBu data, enabled in part by HDSS routine data collected just before the start of this survey (Textbox 1), and the broad consent obtained from participants will allow us to test numerous hypotheses. The broad range of the CoDuBu research framework translates into a broad set of statistical methods. Analytical study plans or project proposals will be developed and submitted to statistical review at participating organizations. Collected data will include continuous and categorical variables. Results from the cross-sectional study will be described accordingly, reporting categorical variables as percentages with 95% confidence intervals, and continuous variables as medians with interquartile ranges. To explore associations between predictors and health outcomes, linear or logistic regression models will be used, as appropriate. Urban and rural differences in associations will be tested, as well as fixed and random effects study area models. Sampling weights will be applied to analyses to ensure a correct representation of the population. Missing data will be reported as separate categories and included in multivariable models. If full case analyses are performed, adjustment for data missingness will be done using appropriate methods for missing data imputation.

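### Hypertension is defined by measured blood pressure alone, so treated participants with readings below 140/90 count as non-cases: prevalence is understated and associations can be biased

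*Protocol article*

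**What the plan says.** Physical Examination in the protocol article describes three seated readings and then the value to be used: "The mean of the last two measurements will be taken for analyses". The case rule follows directly: "Hypertension will be defined as a mean systolic blood pressure ≥140 mm Hg or mean diastolic blood pressure ≥90 mm Hg". Neither current treatment nor a previous diagnosis enters it.

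The textbox of key phenotypes is consistent with this. It lists hypertension prevalence under the physical examination, and lists doctors' diagnoses and treatments as a separate item under the interview.

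The treatment information is collected. Design (Phase II) includes "medication and vaccination history, health care use, as well as knowledge and attitudes regarding NCDs" among the interview topics, and In-Person Interviews adds "family history of disease, medical diagnoses and treatments, vaccination history, and access to health care".

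The rule feeds two parts of the first objective: 1(b), "the prevalence and distribution of metabolic syndrome, hypertension, and diabetes", and 1(c), "the co-occurrence of these IDs and NCDs and the distribution of these comorbidities and their respective risk factors". For associations, Data Analyses says that "linear or logistic regression models will be used, as appropriate".

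**The concern.** Someone with known hypertension who is treated and reads below 140/90 still has the disease that the survey sets out to count. The stated rule puts that person among the non-hypertensive. Three consequences are possible:

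- Hypertension prevalence is too low.
- The proportion with both an infection and hypertension is too low for the same reason.
- In logistic models, some true cases sit in the comparison group. How much this matters depends on whether treatment and control differ between infected and uninfected participants.

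A difference is conceivable here. Under Location, the sites were chosen partly for their degree of urbanization and their malaria and helminth prevalence, and the hospital is in Taabo-Cité. Infection and access to care could therefore both vary by site, and Data Analyses plans to test urban-rural differences in associations.

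**Working it through.** **Inputs from the document.** The case rule is in Physical Examination. The sample of 1020 is in the Abstract and under Sample Size Estimation and Sampling of Participants. The document gives no hypertension prevalence, treated share or control rate, so there is no figure of its own to reproduce.

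**Assumptions.** P is the true prevalence, counting a person as a case if blood pressure is raised or if they are on treatment. f is the share of those cases who are treated and read below 140/90. Both are varied below.

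**Prevalence.** The measured-only rule creates no false positives against this standard and has sensitivity 1 − f. Hence reported prevalence = P(1 − f), and the shortfall = P×f. The 95% half-width, ignoring sampling weights, is 1.96 × √(P(1 − P)/1020). At P = 25% it is 1.96 × √(0.25 × 0.75/1020) = 2.66 points, and true cases number 0.25 × 1020 = 255.

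| f | Reported prevalence | Shortfall (points) | Cases miscoded |
|---|---|---|---|
| 2% | 24.5% | 0.5 | about 5 |
| 5% | 23.75% | 1.25 | about 13 |
| 10% | 22.5% | 2.5 | about 26 |
| 15% | 21.25% | 3.75 | about 38 |

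At P = 25% the shortfall equals the half-width when f = 2.66/25 = 10.6%. Over the wider range P = 15% to 30% and f = 2% to 20%, it runs from 0.15 × 0.02 = 0.3 points to 0.30 × 0.20 = 6.0 points.

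**Co-occurrence.** The same algebra applies within the infected. The reported share with both conditions is the true share times (1 − f₁), where f₁ is the value of f among the infected.

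**Associations.** Let f₁ and f₀ be the values of f in infected and uninfected participants. The observed risks are p₁(1 − f₁) and p₀(1 − f₀), so the observed risk ratio is RR × (1 − f₁)/(1 − f₀), and the observed odds ratio follows from the two observed risks. Take p₀ = 25%. A true odds ratio of 1.5 then gives odds of 0.5 in the infected, so p₁ = 1/3 and RR = 1.333.

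| f₁ / f₀ | Observed OR, true OR 1.0 | Observed OR, true OR 1.5 |
|---|---|---|
| 5% / 5% | 1.00 | 1.488 |
| 10% / 10% | 1.00 | 1.476 |
| 20% / 20% | 1.00 | 1.455 |
| 0% / 10% | 1.148 | 1.722 |
| 10% / 20% | 1.161 | 1.714 |
| 10% / 5% | 0.932 | 1.376 |

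One line worked through, for 0% / 10% under the null: the risks are 0.25 and 0.225, the odds are 0.3333 and 0.2903, and the ratio is 1.148. With equal f the risk ratio stays at 1.333, or at 1.0 under the null.

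**The case against.** **The effect may be small.** Principal Considerations describes an area with little expertise so far and long journeys to adequate care. Health Systems Preparation and Diagnostic Follow-Up reports that hypertension screening equipment and the referral role of the Taabo-Cité hospital came with this project. Few participants may have been treated and controlled before the examination, even in Taabo-Cité. At f = 2% the shortfall is 0.5 points, well inside sampling error. This stands, and it limits the weight of the point.

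**Associations.** A reader might infer that every infection-hypertension association is biased, or that the misclassification is certainly differential. The document supports neither. With equal f the risk ratio is unchanged, a null odds ratio stays null, and 1.5 falls only to 1.476 at f = 10%. No section reports treatment or control by site or by infection status. A hospital in Taabo-Cité shows at most a possible difference between sites, and the planned study-area models would absorb part of one.

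**Timing.** Interviews ran from June to August, after the April and May examinations, and the study paid for the first month of treatment. Nothing shown says that start dates or drug indications were recorded, so some reported medication may have been started because of the study. This calls for care but does not defeat the change. According to the Abstract, participants were referred for blood pressure because it was found to be elevated. If the referral threshold was close to the analysis threshold, nearly all of them are already cases under the measured rule, and counting their medication changes nothing.

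**Condensed article.** An article may leave detail to a fuller protocol or analysis plan. That would excuse silence, but here the case definition is written out. Methods for treated participants in models of continuous blood pressure are analysis-plan detail and form no part of this point.

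**Conclusion.** The point holds in a limited form. As written, the definition counts treated and controlled hypertensives as free of the disease, although the information needed to classify them is collected. Prevalence under objective 1(b), and co-occurrence under 1(c), are understated whenever any true case is treated and controlled. At an assumed true prevalence of 25%, the prevalence shortfall is 0.5 to 3.75 points for f between 2% and 15%, compared with a half-width of 2.66 points. The true size cannot be derived from the document and may lie at the low end.

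For associations the conclusion is conditional. There is slight attenuation of the odds ratio, and none at the null, if f is equal by infection status. Bias in either direction can arise if treatment differs by infection status or by its correlates, such as site and access to care.

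**What to change.** For analysis, define hypertension as mean systolic pressure ≥140 mm Hg or mean diastolic pressure ≥90 mm Hg, or self-reported current antihypertensive medication. Exclude medication started after the Phase I examination where this can be identified. Report the measured-only definition beside it as a sensitivity analysis, labelled as raised blood pressure at examination.

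The cost is about one line in the phenotype definition, with no new measurements. The new definition relies on self-report and on separating earlier treatment from treatment that the study set in motion. Limitations already accepts self-reported history or medication for HIV and tuberculosis, and the separation matters little for those referred because of a raised reading. Where start dates are missing, the write-up should say so, and the gap between the two prevalence figures will show how much depends on the medication criterion. The change affects how participants are classified for analysis and nothing in their care.

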### Laboratory Screening

#### Venous Blood

A total of 7 mL of venous blood was collected in a fasting state for laboratory screening and storage in biobank. Five mL of venous blood (collected using an ethylenediaminetetraacetic acid [EDTA] tube) was used for the assessment of glucose, HbA1c, lipids, as well as for assessment of *Plasmodium*, and anemia. HemoCue Glucose 201 RT device was used to measure fasting glucose (HemoCue AB) and was calibrated regularly. Afinion AS100 Analyzer (Alere GmbH) was used as the point-of-care test for HbA1c (where the method has been validated for HbA1c testing in settings with high prevalence of hemoglobinopathies) and lipid profile (total cholesterol, low-density lipoprotein cholesterol, high-density lipoprotein cholesterol, and triglycerides). Afinion test kits were stored at 4°C, with regular calibration of the analyzers. For assessment of *Plasmodium* infection, thick and thin blood films were prepared on microscope slides. For the diagnosis of *Plasmodium*, the slides were air-dried, stained with Giemsa, and examined under a microscope by experienced laboratory technicians for *Plasmodium* species identification and parasitemia. The number of parasites was counted against 200 leukocytes or 500 leukocytes if number of parasites was ˂10, assuming a standard count of 8000 leukocytes per μl of blood [62]. Additionally, a drop of blood was subjected to a rapid diagnostic test for malaria using ICT ML01 malaria Pf kit (ICT Diagnostics). Anemia was indirectly assessed by the hemoglobin level, using HemoCue Hb 301 device (HemoCue AB), adhering to World Health Organization recommendations [63]. The remaining EDTA-buffered blood was processed into the biobank.

Two mL of venous blood (collected using a dry tube) was used to prepare DBS on custom printed diagnostic cellulose filter paper (Whatman) for DNA methylation profile and neonatal Guthrie cards for cytokine profiles.

Key health-related phenotypes in the CoDuBu study investigating the co-occurrence of common infectious diseases and noncommunicable diseases in Côte d’Ivoire.**A. Key phenotypes from the physical health examination:**Distribution of body temperature (auricular temperature)Distribution of height, weight, waist and hip circumference, prevalence of obesityDistribution of blood pressure and heart rate and prevalence of hypertension**B. Key phenotypes from the laboratory screening:**Prevalence of *Plasmodium* infectionPrevalence of urogenital schistosomiasis (*Schistosoma haematobium*)Prevalence of intestinal schistosomiasis (*S. mansoni*)Prevalence of species-specific soil-transmitted helminths (*Ascaris lumbricoides*, hookworm and *Trichuris trichiura*)Prevalence of *Strongyloides stercoralis*Prevalence of anemiaPrevalence of prediabetes/diabetesPrevalence of dyslipidemia**C. Key phenotypes from interview (>200 variables covering risk factors and effect modifiers):**Prevalence of doctor’s diagnoses/treatments, including HIV, tuberculosisPrevalence of health symptoms related to cardiovascular diseases, diabetes, respiratory diseases, and infectious diseasesDistribution of access to quality careDistribution of knowledge related to noncommunicable diseases and risk factorsPrevalence/exposure to noncommunicable disease risk factors: tobacco smoking, physical activity, nutrition, alcohol consumption, environmental exposures (air pollution from fossil fuels, occupational exposures, noise annoyance), gender/reproductive factors, stress, resilience, depression, and other psychosocial factors**D. Other variables derived from the Taabo health and demographic surveillance system database:**Sociodemographic factors (age, sex, nationality, ethnicity, marital status, pregnancy history, educational level, occupation, socioeconomic status assessed by a household-based asset index)Household characterization (size, water supply, sanitation and cooking facilities, building characteristics, and residential history)**E. Biobank:**Dried blood spots/aliquots from venous blood: genetic variation, DNA methylation, cytokine profileStool: gut microbiomeUrine: metabolome

#### Urine Sample

A midstream morning urine sample was collected using BD Vacutainer system (Beckton, Dickinson & Co) and transferred to the laboratory for processing. Nine mL of urine was taken from the vacutainer using a separate vacuette, which was later processed into the biobank. A small amount (10-20 µl) of urine was used for the detection of *S. mansoni*, using the point-of-care circulating cathodic antigen cassette (ICT Diagnostics), following the manufacturer’s instructions [64], resulting in the following classification: negative or three levels of positives (1+, 2+, or 3+). Dipstick urinalysis to detect proteins, blood, glucose, urobilinogen, bilirubin, leucocytes, ketones, nitrites, pH, and specific gravity was applied using the Roche Combur-10 test (Roche Diagnostics). Urine samples testing positive for blood were subjected to filtration test for the diagnosis of *S. haematobium.* Positive results were expressed as the number of *S. haematobium* eggs per 10 mL of urine, according to World Health Organization guidelines [65].

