**Methods:**

A baseline cross-sectional population-based survey was conducted over one year, in the Taabo health and demographic surveillance system (HDSS) in south-central Côte d’Ivoire. We randomly identified 1020 consenting participants aged ≥18 years in three communities (Taabo-Cité, Amani-Ménou, and Tokohiri) reflecting varying stages of epidemiological transition. Participants underwent health examinations consisting of NCD phenotyping (anthropometry, blood pressure, renal function, glycemia, and lipids) and infectious disease testing (infections with soil-transmitted helminths, schistosomes, and Plasmodium). Individuals identified to have elevated blood pressure, glucose, lipids, or with infections were referred to the central/national health center for diagnostic confirmation and treatment. Aliquots of urine, stool, and venous blood were stored in a biobank for future exposome/phenome research. In-person interviews on sociodemographic attributes, risk factors for infectious diseases and NCDs, medication, vaccinations, and health care were also conducted. Appropriate statistical techniques will be applied in exploring the concomitance of infectious diseases and NCDs and their determinants. Participants’ consent for follow-up contact was obtained.

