### Design

This was a population-based cross-sectional study among adult participants aged ≥18 years, randomly sampled within the selected Taabo HDSS areas. The examinations and interviews were conducted between April and August 2017. A biobank was established for future biomarker research based on biospecimens collected from the participants. The survey occurred in two phases.

Phase I (health examination; April and May 2017) took place over 2 days for each participant. The first day included obtaining informed consent, provision of materials and instructions for biospecimen collection (clean plastic container and OMNIgene.GUT tube (DNA Genotek Inc) for stool and BD Vacutainer urine collection system (Beckton, Dickinson & Co) for urine, at participants’ residences. The next morning, while participants underwent health examinations (at the health center) in a fasting state, fresh morning stool and urine samples collected at home were transferred cooled (~4°C) to the Taabo-Cité central laboratory for immediate pre-analytic processing. In the field, health examinations included point-of-care glucose, hemoglobin, HbA1c, lipids tests, anthropometry (height, weight, neck, arm, waist, and hip circumference), blood pressure, pulse, temperature, as well as preparation of dried blood spots (DBS) on filter papers. At the end of the examination, blood sample (stored at 4°C within 10 minutes of venepuncture) and DBS were sent to the laboratory for further processing. Multimedia Appendix 1 shows the detailed flow of the health examination in the field.

In the laboratory, blood samples were applied towards malaria diagnoses (rapid test and microscopy) and further aliquoted and stored (together with the DBS) in a -80°C biobank. Stool from the plastic container was analyzed for helminth eggs (or larvae), and urine was subjected to *S. mansoni* test and dipstick urinalysis (for blood, proteins, blood, glucose, urobilinogen, bilirubin, leucocytes, ketones, nitrites, pH, and specific gravity). Urine samples that tested positive for blood underwent a filtration method for *S. haematobium*. The remaining urine and OMNIgene.GUT-stabilized stool were aliquoted and transferred to the -80°C biobank. Case reporting and management of diagnosed IDs and NCDs were incorporated within the health examination period (Figure 3). Multimedia Appendix 2 shows the detailed flow of the laboratory work.

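### *S. haematobium* is sought only in urine that is dipstick-positive for blood, so its full-sample prevalence is a lower bound and its egg intensity is known only for participants with haematuria

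*Protocol article*

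**What the plan says.** Two sections of the protocol article give the same rule. Under Urine Sample: "Urine samples testing positive for blood were subjected to filtration test" for *S. haematobium*. Under Design: "Urine samples that tested positive for blood underwent a filtration method for" that species. A positive result is then quantified: "Positive results were expressed as the number of" eggs per 10 mL of urine. The antigen cassette applied to urine is described for *S. mansoni* only.

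The other helminths have no such precondition. Under Stool Samples, Kato-Katz smears are made from every stool sample, and the Baermann technique for *S. stercoralis* is described without a prior screen.

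Objective 1(a) is to assess "the prevalence, intensity, and distribution of helminth" infections and lists *S. haematobium* among them. Objective 1(c) covers "the co-occurrence of these IDs and NCDs and the distribution of these comorbidities and their respective risk factors at the level of individuals". Textbox 1 lists the prevalence of urogenital schistosomiasis as a key phenotype, with no qualifier.

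Data Analyses does not say how urine that was never filtered is classified. The nearest statement is "Missing data will be reported as separate categories and included in multivariable models". Limitations discusses sample size and the absence of HIV and tuberculosis testing, but not the dipstick step.

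**The concern.** The measurement rule cannot deliver the estimate that the objective promises. An infected participant with a blood-negative dipstick never reaches the test that would find the infection. A full-sample prevalence is then too low by the share of infections without dipstick haematuria, and intensity describes only infections that came with blood in the urine. Published without a qualifier, the figure would be read as population prevalence and compared with ungated figures for the other helminths.

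A second, conditional problem touches objective 1(c). Whether a person is tested depends on haematuria. If haematuria from causes other than the parasite is more common in people with an NCD, or in one sex, the chance of detecting an infection depends on the very variable with which it will be associated.

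**Working it through.** **Inputs from the article.** Filtration only after a positive blood dipstick (Design; Urine Sample); 1020 participants; assumed diabetes prevalence 6% (Sample Size Estimation). The article gives no *S. haematobium* prevalence, dipstick sensitivity or haematuria rate, so there is no stated figure to reproduce.

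**Assumptions.** True prevalence π = 5%; dipstick sensitivity in infected people s = 50% to 90%; filtration itself without error.

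**1. Prevalence with all participants as denominator.** Observed prevalence = π × s, which cannot exceed π. Infections present: 1020 × 0.05 = 51.

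| s | Observed prevalence | Infections missed, 51 × (1 − s) |
|---|---|---|
| 0.5 | 2.5% | 25.5 |
| 0.7 | 3.5% | 15.3 |
| 0.9 | 4.5% | 5.1 |

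The relative loss, 10% to 50%, does not depend on π.

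**2. Association, true odds ratio 1, unfiltered urine counted as negative.** Let NCD-related haematuria bring a proportion x of otherwise dipstick-negative infected people to filtration. Detection is s without the NCD and s + (1 − s)x with it. Apparent OR = odds(π[s + (1 − s)x]) / odds(πs), with π = 5%.

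| s | x = 5% | x = 10% | x = 20% |
|---|---|---|---|
| 0.5 | 1.05 | 1.10 | 1.21 |
| 0.7 | 1.02 | 1.04 | 1.09 |
| 0.9 | 1.01 | 1.01 | 1.02 |

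Example for s = 0.5, x = 20%: (0.03/0.97) / (0.025/0.975) = 1.21. Allowing 5% background haematuria without the NCD, against 10%, 15% or 25% with it, gives nearly the same range: 1.01 to 1.20 at π = 5%, and at most 1.22 at π = 20%.

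**3. Association, true odds ratio 1, filtered samples only.** Let h be haematuria from other causes (h₀ without the NCD, h₁ with it) and d = 1 − (1 − s)(1 − h) the detection probability (d₀, d₁). The odds of infection among filtered samples are πd / [(1 − π)h], so π cancels and OR = (d₁/d₀) × (h₀/h₁). With h₀ = 5% and s from 0.5 down the range to 0.9:

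- h₁ = 10%: 0.52 to 0.50
- h₁ = 15%: 0.37 to 0.34
- h₁ = 25%: 0.24 to 0.20

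Example for s = 0.5, h₁ = 10%: (0.55/0.525) × (0.05/0.10) = 0.52. Putting unfiltered urine in a separate missing category leads to the same place: in an unadjusted model, the contrast of egg-positive with filtered egg-negative is this odds ratio. Prevalence among filtered samples would also be greatly inflated: at π = 5% and h = 5% it is 36% for s = 0.5 and 49% for s = 0.9.

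**4. No difference in other haematuria by NCD status.** A true null stays at 1. With all participants analysed, a true OR of 2 is only attenuated, to between 1.80 and 1.99 for π from 5% to 20%.

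**The case against.** Four objections deserve an answer.

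*No documented link between NCD and haematuria.* A reader might infer that the associations with hypertension and diabetes are biased through kidney damage. The article does not support that as a fact. It links neither disease to haematuria and gives no haematuria rate; the Abstract only lists "NCD phenotyping (anthropometry, blood pressure, renal function, glycemia, and lipids" among its measures. This stands, and the association part must remain conditional. The same holds for sex.

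*Coding is a matter for the analysis plan.* The article nowhere says that unfiltered urine counts as uninfected, and it promises analytical plans with statistical review. This also stands: lower bound holds only with all participants as denominator, and the direction of any association bias depends on the coding. The restricted testing, however, is a stated measurement rule that has already been applied. No later coding choice recovers the undetected infections.

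*The possible bias is small beside random error.* At π = 5% and s = 0.7 about 36 infections are detected. With diabetes at 6%, about 2 co-occurrences are expected under independence, and the 95% interval for the odds ratio spans roughly a factor of 4 either way. For an assumed NCD prevalence of 25% the factor is about 2.2. Against this, a shift of 1.01 to 1.21 changes little, which argues for a short sensitivity analysis and no more. It does not excuse an analysis of filtered samples only, where the shift is of an entirely different order.

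*Limited reach.* *S. haematobium* is one of six helminths, and the sample size reasoning rests on malaria with diabetes and with HbA1c. Both are untouched, which limits the priority of the point.

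Three further inferences should be avoided. The detected infections are not necessarily symptomatic, because a dipstick result is a laboratory sign. That mean intensity is overstated assumes that heavier infections bleed more, which the article does not say. No combined any-helminth variable is defined to which the error could carry over.

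**Conclusion.** The core holds on the article's own text. Filtration was confined to blood-positive urine, no other *S. haematobium* test is described, and the promised prevalence carries no qualifier. With all participants as denominator it is a lower bound, apart from false-positive filtration; an assumed 5% becomes 2.5% to 4.5% at an assumed dipstick sensitivity of 50% to 90%. Intensity is known only for the haematuric subset.

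The association part holds only conditionally. If haematuria from other causes differs by NCD status, a true null would appear as about 1.01 to 1.21 when unfiltered urine counts as negative, and as about 0.20 to 0.52 under the rates assumed above when only filtered samples are used. Without such a difference there is no spurious association. The point should be acted on because the correction is cheap, but it concerns one infection and does not threaten the study's main malaria questions.

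**What to change.** - In the Objectives and Textbox 1, relabel the phenotype as *haematuria-screened, filtration-confirmed S. haematobium (lower bound)*, and state that egg intensity refers to blood-positive urine only.
- Use all participants with a dipstick result as the denominator. Do not describe unfiltered urine as confirmed negative, and do not restrict association models to filtered samples.
- Report prevalence over a stated range of dipstick sensitivity (observed prevalence divided by s).
- Add a short sensitivity analysis of the *S. haematobium*–NCD associations in which detection differs by NCD status.
- Name the dipstick restriction in Limitations.

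Recruitment is complete, so this is a matter of reporting and analysis and needs no new samples. The cost is that the headline prevalence becomes a bound, with a little extra analysis.
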